### The Get Healthy, Stay Healthy (GHSH) intervention

The 6-month GHSH extended contact intervention is primarily delivered via text messages that are individually-tailored in terms of frequency, timing, content and wording. In order to tailor the text message content and to negotiate the participant’s text messaging preferences, participants receive two tailoring telephone calls; one call at the start of the intervention; and another call at mid-intervention (Figure 1). During the GHSH extended contact intervention participants choose whether they focus on a weight loss (no more than 2 kg per month) or weight maintenance goal and whether they focus on physical activity or diet or both behaviours (with targets consistent with national guidelines for physical activity and healthy eating [36,38]). This flexible, tailored approach to intervention targets is in line with the GHS coaching program.

**Figure 1 F1:**
[figure not shown]
Overview of the Get Healthy, Stay Healthy intervention protocol.

#### Initial tailoring call

This 20–30 minute telephone call gathers information in order to tailor the text messages and is guided by a script. The call starts by reviewing what participants have achieved (in regards to their physical activity, diet and weight) during the GHS (this information is provided by the GHS coaching staff). Participants are asked to reflect on what they have achieved, what worked, and did not work to support them during their involvement in the GHS. They are guided to set two SMART (specific, measureable, achievable, realistic, time-based) goals for behaviour change (physical activity, diet or both) to achieve in the next 3-months. For each SMART goal, participants identify: a self-selected reward for reaching their goal; benefits they expect to experience if they reach their goals; preparatory behaviours to help reach their weekly goals; barriers and solutions to overcome them; and, a person who could support them to reach their goal and what specific action this person could take. Finally, participants select the number, timing and type of text messages they would prefer to receive for the first three months of the program. All of this information is recorded during the call and is used to tailor the content, timing and frequency of the GHSH text messages. In this study, the tailoring telephone calls are conducted by health coaches trained in behaviour change and motivational interviewing. However, ideally, when the GHSH extended contact intervention is taken up as part of the larger GHS; the GHS coach would conduct these two tailoring calls.

#### Get Healthy, Stay Healthy text messages

Participants select the number of text messages (within the range of three to 13 per fortnight), timing of texts (e.g. 6:00 am), and type of texts (e.g. optional texts about prompting preparatory behaviours). The texts reinforce behaviour change strategies discussed in the GHS (e.g., barrier identification, goal setting), as well as those shown in previous research to be important for maintaining behavioural changes: self-monitoring [10,39-41]; increased awareness of and satisfaction with positive outcomes of behavioural change [42-44]; environmental cues to behaviours [42,45,46]; and, self-regulation skills [47-49]. Wording of the text messages is tailored to individuals based on their: name, gender, long-term weight goals for next 3-months, short-term behavioural goals for next week, identified barriers and strategies to overcome them, preparatory behaviours to achieve their goals, perceived expectations of behavioural change and the name of a person who can provide them with social support to achieve their goals. All texts are signed off using the first name of the GHSH coach the participant spoke to during the initial tailoring call. GHSH text messages are limited to 160 characters. The content of the texts refers participants back to existing GHS infrastructure such as the paper-based weight tracker. The abbreviations used in the GHSH text messages are based on previous research with community samples on the comprehension of text message language [50].

There are four types of GHSH text messages that each target different behaviour change strategies and each have different minimum frequencies (Table 1). Firstly, all intervention participants receive a prompt to self-monitor their weight at least once per fortnight. Participants are not asked to report their weight via text message but simply prompted to weigh themself and record it in their GHS weight tracker. Second, participants receive a goal check text message at least once per fortnight that checks whether they met each of their behavioural goals in the past week. These goal check texts ask participants to reply ‘yes’ or ‘no’ to indicate their goal attainment. This reply option is voluntary and participants incur the costs of reply texts. Based on the participants’ reply they will receive a tailored goal check reply text message. These replies are often tailored to the participants’ anticipated outcomes of reaching their goals (see Table 1). The third type of text is a real-time behavioural prompt, which is optional and capped at a maximum of four per fortnight. These texts aim to remind participants of their SMART goals, preparatory behaviours and anticipated barriers and solutions to overcome them. The final type of GHSH text is sent once in Week 6 and Week 18 and it prompts participants to reflect on their weight and behavioural goals and re-set them appropriately. Participants are encouraged to let their GHSH coach know their new goals via reply text and these changes are reflected in subsequent text messages.

**Table 1 T1:** Examples of the four types of Get Healthy, Stay Healthy text messages

**Text message type**	**Behaviour change strategies targeted**	**Example text messages**	**Minimum frequency**
**Self-monitoring of weight**	Self-regulation; Satisfaction with perceived outcomes	Take time today 2 weigh yourself Bob. It will help u c how ur tracking to lose another 2 kg & make u think about ur diet & exercise. Jenny	1 per fortnight
**Goal check of behavioural goals**	Self-regulation; Satisfaction with perceived outcomes	Hi Bob. Did u reach ur exercise goal 2 walk 30 mins x 4 times this week? Text me back yes or no so I know how ur going. Jenny	1 per fortnight for each behavioural goal
	Self-regulation; Outcome expectancy; Satisfaction with perceived outcomes; Self efficacy; Social Support	Congratulations on reaching ur weekly goal Bob. U need 2 reward ur efforts. Ur reward was 2 catch up with friends. Jenny	Only sent if participant responds to goal check
**Prompting behavioural cues**	Self-regulation; Perceived environmental opportunity; Self efficacy; Social Support	Bob u planned 2 walk today after work. Try putting ur exercise clothes on as soon as u get home & dont change until u have been 4 ur walk. Jenny	Optional (maximum 4 per fortnight)
		I know breakfast is hard 4 u 2 fit in. Set ur alarm 10 mins earlier or find a nutritious option 2 eat on the run. Bob this is important 4 ur health. Jenny	
**Goal re-set**	Self-regulation	Its important 2 re-set ur weight goal Bob. U currently want 2 lose another 2 kg. If u have a new goal 4 the next 6 weeks, reply & let me know. Jenny	Once in Week 6 and 18

Text messages are generated and sent by research staff, using a purpose-designed software package in which messages are able to be pre-programmed in advance and scheduled to be sent at specific times (e.g. Monday morning at 7 am). The software interfaces with a database of 115 pre-written text message frameworks, which each contain words and phrases that can be tailored based on the participant’s individual data. When developing these text message frameworks, each message was systematically mapped on to at least one of the targeted behaviour change strategies (as previously listed). Replies to the goal check texts are stored and the tailored response automatically triggered if the participants reply with the words ‘yes’ or ‘no’ (or accepted variations of these such as ‘nah’ etc.). If participants reply to a goal check with additional words (e.g. providing a justification as to why they did not meet their weekly goal) or a word not identified as a variant of ‘yes’ or ‘no’, then the program sends an email to research staff for them to manually decide which tailored goal check reply (met goal or did not meet goal) to send to the participant. Unprompted reply text messages from participants do not receive a reply and participants are made aware of this. At any stage the participants can change their text message preferences, behavioural or weight goals or withdraw from the study by contacting research staff via text message or telephone call. Any changes made to goals or text preferences are entered into the software program as soon as possible and subsequent texts incorporate these changes.

#### 12-week tailoring call

At three months (12-weeks) participants receive a telephone call to facilitate tailoring of texts based on updated information for the final three months of GHSH. The call is designed to last approximately 20 minutes and is guided by a script. This call follows a similar framework to the initial tailoring call and collects the same list of information for each of the two SMART goals (e.g. expected outcomes, barriers etc.). The protocol for this call stipulates that it should be made between Weeks 12 and 14, and if contact is not made during this period, the existing tailoring information is carried over for the final 3-months of the text messages.

### Control group treatment

The control group receives no contact, except for the evaluations at baseline, 6- and 12-months. Following completion of each assessment, control group participants are posted brief written feedback on their results to reduce attrition.

### Data collection

Data are collected from participants at baseline, 6-months (end of extended contact intervention) and 12-months (follow-up after 6-months of no contact). To enable comparison to outcomes from the broader evaluation of the GHS, the anthropometric and behavioural measurement tools used in this study are the same as those used in the GHS evaluation. In addition to these GHS-comparable measures, we are also collecting more detailed data on moderate-vigorous physical activity (via accelerometer) and dietary behaviours (via the Fat and Fibre Behaviour Questionnaire). Objective assessment of anthropometric outcomes (i.e. body weight, waist circumference) was not possible due to the cost of collection from study participants who could reside anywhere within the state of New South Wales.

At each assessment participants complete a computer-assisted telephone interview (CATI) conducted by a trained research assistant, fill out a paper-based questionnaire and wear an objective activity monitor. Participants in this study had previously completed pre- and post-GHS evaluations therefore, demographic data and data on change in primary outcomes during the initial GHS were not re-assessed in this protocol. The assessment tools employed are summarised in Table 2.

**Table 2 T2:** Summary of outcomes and measures used in the Get Healthy, Stay Healthy trial

**Primary outcomes**	**GHS-comparable tools**	**Additional tools**
Moderate-vigorous physical activity (MVPA)	● 3-item physical activity assessment tool [51] capturing walking, moderate and vigorous activity (via CATI)	● Accelerometer (Actigraph GT1M, 10s epoch) capturing duration and frequency of MVPA
Dietary behaviours	● Two stand-alone items [56] on servings of fruit and vegetables per day (via CATI)	● Fat & Fibre Behaviour Questionnaire [58] via CATI (Total Index (1 to 5))
Body weight and waist circumference	● Self-reported (via CATI)	
**Secondary outcomes**	**GHSH-specific tools**	
Feasibility indicators	● Number and type of text messages sent	
	● Number and duration of tailoring interviews completed	
	● Number of prompted and unprompted text message replies from participants	
Acceptability indicators	● Recall of number of text messages received	
	● Treatment of text messages on receipt	
	● Categorical satisfaction ratings	
	● Qualitative feedback on intervention	
Mediators	● Outcome expectancy: MVPA [60]; diet [64]	
	● Satisfaction with perceived outcomes: MVPA and diet [59]	
	● Self-regulation: MVPA and diet [65]	
	● Self-efficacy: MVPA [66]; diet [67]	
	● Social support: MVPA and diet [68]	
	● Perceived environmental opportunity: MVPA [69]; diet [72,73]	
Moderators	● Demographics (e.g. age, education)	
	● Health status (e.g. chronic diseases, need for medical clearance before commencing GHS)	
	● Behavioural and anthropometric changes during initial GHS	

### Primary outcomes

#### Moderate-vigorous physical activity

At each assessment, participants complete a self-reported physical activity measure [51] during the CATI. This is a validated, 3-item assessment tool (3Q-PA) which asks participants to report the number of weekly sessions spent: walking for ≥30 minutes; doing moderate-intensity physical activity for ≥30 minutes; and, doing vigorous-intensity physical activity for ≥20 minutes. These sessions were summed to indicate the total number of health-enhancing physical activity sessions per week.

In addition to the self-reported measure, participants are posted a dual-axis accelerometer (Actigraph model GT1M; Actigraph, LLC, Fort Walton Beach, Florida), initialised to collect data in 10-second epochs, and a wear-time log. The wear log includes monitor fitting instructions and asks about any monitor removals, sleep time and whether the monitor was worn or removed during sleep. Before posting, research staff telephone the participant to negotiate a start date and reiterate the instructions from the wear-time log: to fit the accelerometer by elasticised band firmly around the waist at the right mid-axillary line; to wear the monitors continuously during all waking hours and to remove for any water-based activities that may damage the monitor. On the (expected) second day of wear, a follow-up telephone call is made by research staff to prompt participants to wear the monitor if they have not already done so and to return their accelerometer return when finished in a reply-paid envelope.

Accelerometer data are downloaded in Actilife (v 6.6.2) as both 10-second and 60-second epoch files and will be processed in SAS version ≥9.3 by a variety of methods. The main measures will be derived from the 60-second data using Freedson cutpoints (i.e., 1952 counts per minute [cpm] for moderate and 5724 cpm for vigorous) [52] as these are the most common of the validated approaches. Secondary approaches will include: a very low and very high cutpoint for moderate-vigorous activity [53,54] and Crouter’s two-step regression to ensure conclusions are robust to choice of cutpoint and use of a cutpoint-based versus variability-based approach. Analyses will be limited to days with ≥10 hours of wear and no excessive counts ≥20, 000 cpm (valid days). Bouts of ≥60 minutes of 0 cpm (allowing for < 3 minutes of counts 1–49 cpm) will be excluded as non-wear time [55]; self-reported sleep time will also be excluded for those wearing the monitor to bed. Outcomes used from the accelerometer data will include: average minutes per valid day of moderate-vigorous activity; and, average number of bouts per valid day of moderate-vigorous activity accumulated in ten minutes bouts (allowing for two one-minute epochs below this threshold).

#### Dietary behaviours

Participants are also asked the questions currently asked in the GHS evaluation via CATI. These questions ask participants to report their number of servings of fruit per day and vegetables per day [56]; and to report their average consumption of sweetened drinks per day (cups/day); and, takeaway meals per week (meals/week) [57].

Participants also complete the Fat and Fibre Behaviour Questionnaire (FFBQ) [58] during the CATI. This questionnaire assesses eating habits over the previous month. Nine items, scored from 1 (‘6 or more days per week’) to 5 (‘Never’), relate to consumption of particular high-fat or high-fibre foods. The remaining items, scored from 1 (‘Never’) to 5 (‘Always’), ask about behaviours related to cooking, eating or choice of foods. The three indices from the FFBQ (Total Index (20-items), Fat Index (13-items) and Fibre Index (7-items)) were responsive to change in our previous trials [59]. The indices have good two-week test-retest reliability (ICC = 0.87- 0.89), Pearson’s correlations of 0.50-0.56 with fat and fibre intake assessed by Food Frequency Questionnaire and similar or higher responsiveness compared to the Food Frequency Questionnaire [58]. The primary index of interest for this study will be the Total FFBQ Index (range 1–5).

#### Anthropometric outcomes

Body weight and waist circumference are self-reported by participants at each assessment point during the CATIs. Participants are asked to report their body weight in kilograms, measured whilst wearing light clothes and no shoes. They were encouraged to weigh themselves at the time of the interview if scales were present; otherwise they were asked to report their most recent weighing. Participants also report their waist circumference in centimetres during the CATI. Participants are posted a measuring tape and instruction sheet (with images) at baseline. The CATI interviewer instructs participants to take this measurement during the call, guiding them to measure from the top of their hip bone and to keep the tape straight. A validation sub-study of GHS participants (n = 38) revealed that self-reported weight was 1.6 kg (95% CI: 0.8 to 2.4 kg) lower than objectively measured weight [33]. There was 87% agreement between self-reported and objectively measured waist circumference classifications [33]. Body Mass Index (BMI) will be calculated based on participant’s self-reported height at baseline and their self-reported weight at each assessment point.

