## Background

Overweight and obesity, along with insufficient physical activity and unhealthy dietary intake are associated with considerable burden of disease [1,2]. Over 60% of Australian adults are overweight or obese, 62% do not meet national physical activity guidelines and the vast majority do not meet dietary guidelines [2]. These population rates are similar to those in comparable developed countries [3-6]. While multi-sectoral approaches addressing policy, practice and social-environmental factors are needed to tackle obesity at a population level, there remains a need for effective broad-reach, individual-level interventions to support those adults who are currently overweight or obese (estimated nine million Australians) [7] to achieve and maintain moderate weight loss through health behaviour change.

Behavioural lifestyle interventions are effective at promoting initial weight loss [8,9]. However, maintaining improvements in these outcomes is often more difficult to achieve. Evidence indicates an average regain of 0.3 kg per month following the end-of-intervention [10,11], with the average participant regaining approximately 30% to 35% of their weight lost in the first year [12]. Within one [13] to five years [12,14] post intervention, 50% or more of participants are likely to have returned to their baseline weight. The challenge in maintaining weight loss post-intervention has been largely attributed to the failure in maintaining physical activity and dietary behaviour change [14,15].

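### The fallback for self-reported weight has no age limit and only the intervention arm is prompted to weigh, so the age of the 6-month weight can differ by arm

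*Protocol article*

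**What the plan says.** All places are in the Protocol article.

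- **Anthropometric outcomes.** "Body weight and waist circumference are self-reported by participants at each assessment point during the CATIs". Participants are encouraged to weigh themselves during the call "if scales were present; otherwise they were asked to report their most recent weighing". Clothing and footwear are specified, but the age of the fallback weight is not. Waist is handled differently: it is measured during the call with a tape posted at baseline.
- **Get Healthy, Stay Healthy text messages.** "all intervention participants receive a prompt to self-monitor their weight at least once per fortnight". These weights do not reach the trial: "Participants are not asked to report their weight via text message but simply prompted to weigh themself and record it in their GHS weight tracker".
- **Control group treatment.** "The control group receives no contact, except for the evaluations at baseline, 6- and 12-months".
- **Data collection.** Months 6 to 12 are free of contact, so the prompts have ended well before the 12-month assessment.
- **Background.** "Evidence indicates an average regain of 0.3 kg per month following the end-of-intervention".
- **Sample size.** Small further improvement is expected in GHSH from baseline to 6 months, and decline in controls. The weight difference of interest is 2 kg, with SD 16.5 kg and pre-post correlation 0.97.

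**The concern.** The intervention acts on how the outcome is measured as well as on the outcome. A GHSH participant with no scales at hand during the 6-month call has been prompted to weigh within the last fortnight or so. A control in the same position has had no prompt since baseline and may give a weight that is weeks or months old. If controls are regaining, that older weight is too low, and the between-arm difference is understated.

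The validation figure in the same section (self-report 1.6 kg below measured weight, n = 38) comes from GHS participants taken together. It cannot show whether reporting error differs between these two arms.

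At stake is a missed or diluted weight effect at 6 months, the time point for which the trial was sized. A second, weaker consequence concerns the planned comparison of 6 with 12 months. Once prompts stop, GHSH fallback weights may become older, and regain after the intervention could then be understated in that arm.

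**Working it through.** **Inputs from the article:** difference of interest 2 kg; SD 16.5 kg; correlation 0.97; 106 per group; 20% attrition; two-sided 5%; regain 0.3 kg per month.

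**Inputs assumed, because the article does not give them:** the share of participants at 6 months whose weight is a fallback (f, taken as equal in both arms), and how many months older control fallback weights are than GHSH ones (a).

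**Step 1: the plan's own figures.** The size is set by self-reported activity (difference 2, SD 5.7, r 0.70). The baseline-adjusted SD is 5.7 × √(1 − 0.70²) = 4.071, which needs 88 per group for 90% power. 88 × 1.2 = 105.6, so the stated 106 is reproduced. After 20% attrition, 106 × 0.8 = 84.8, about 85 completers per group.

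For weight, the adjusted SD is 16.5 × √(1 − 0.97²) = 4.011 kg. With 85 per group and a 2 kg difference, power is 0.902. The claim of at least 90% for weight is reproduced, with nothing to spare.

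**Step 2: bias from unequal age.** Bias = f × a × 0.3 kg per month, toward no difference. The difference seen is 2 minus the bias.

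| Share f | Extra age a (months) | Bias (kg) | % of 2 kg | Difference seen (kg) | Power, 85 per group |
|---|---|---|---|---|---|
| 0 | – | 0 | 0 | 2.00 | 0.90 |
| 10% | 1 | 0.1 × 1 × 0.3 = 0.03 | 1.5 | 1.97 | 0.89 |
| 20% | 2 | 0.2 × 2 × 0.3 = 0.12 | 6 | 1.88 | 0.86 |
| 30% | 3 | 0.3 × 3 × 0.3 = 0.27 | 13.5 | 1.73 | 0.80 |
| 50% | 3 | 0.5 × 3 × 0.3 = 0.45 | 22.5 | 1.55 | 0.71 |

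The first three non-zero rows are a moderate range. The last needs half of all participants to use the fallback and control weights three months older, and is shown only as an outer case.

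**Step 3: where it applies.** At baseline neither arm has had a GHSH prompt, so no difference in age is expected. At 6 months GHSH has had six months of prompts and controls none. At 12 months prompts have been off for six months, and any between-arm gap would rest on habit alone.

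**The case against.** The strongest reply is that the mechanism partly defeats itself. Anyone with scales at hand is encouraged to weigh during the call in either arm, and someone with no access to scales cannot act on a prompt. This stands, and it narrows the affected group. It does not empty it: the rule turns on scales being present at the call, and weighing then is only encouraged. People called away from home, people who weigh elsewhere and people who decline to weigh during the call can all give an older weight, and prompts can keep that weight recent in one arm only.

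Further points stand:

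- Controls have just finished coaching and have access to the same paper tracking tools, so some will weigh often.
- The 0.3 kg per month is a general literature rate. The Background also reports some maintenance of weight loss six months after GHS in a small sub-sample, so drift may be slower.
- Bias toward no difference cannot by itself produce a false claim of benefit. It can still hide a real one, in a trial meant to inform GHS delivery.
- An article condenses its protocol. The interview script may already record the date and source of each weight, and their absence here is not an error. The point rests on the fallback rule as stated.

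A reader might infer that the age of the weights does differ by arm and does bias the result. The documents do not support that, since they give neither the share affected nor any ages. A reader might also infer that weights older than a few days should be refused. That could do harm: prompted participants are more likely to hold a recent weight, so an exclusion rule could create missing data that depend on arm.

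**Conclusion.** The point holds as a risk built into a stated rule. The fallback for a primary outcome has no age limit, and the intervention can itself change how recent that weight is, chiefly at 6 months. On the article's expectations the bias is toward no difference. Over moderate assumptions it is about 0.03 to 0.27 kg of the 2 kg difference of interest, taking weight power from about 0.90 to between 0.89 and 0.80. This rests on assumed shares of 10–30%, assumed extra ages of 1–3 months, an equal fallback share in both arms, and 0.3 kg per month applying to the participants concerned. The true size may be negligible. The case for acting is that the repair is cheap and that, unless date and source are recorded, the bias can be neither measured nor ruled out afterwards.

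**What to change.** 1. At the remaining 6- and 12-month interviews, record whether the weight was taken during the call and, if not, the date of the weighing.
2. In both arms, ask anyone without a same-call weight to weigh and report it at the accelerometer follow-up call that staff already make (Moderate-vigorous physical activity section).
3. Keep all reported weights in the main analysis.
4. Add a sensitivity analysis restricted to in-call or recent weights, or adjusting for the age of the weight, and report the age of weights by arm at each time point.

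**Cost.** Two extra interview items and one question on an existing call. The restricted analysis may select participants differently by arm, so it should stay a sensitivity analysis and not become an exclusion rule.
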